
### Secondary outcome measures

The secondary outcome measures include psychometric features of anxiety and depression, pain catastrophizing, and kinesiophobia, and also the adherence of patients to treatment sessions.

Hospital Anxiety and Depression Scale (HADS) will evaluate anxiety and depression. This questionnaire comprises 14 items and two subscales (anxiety and depression). Each subscale consists of 7 questions. Each item is scored on a 4-point scale. The total score ranges from 0 to 21. A subscale score of more than 8 denotes anxiety or depression. The Persian version of HADS is a valid and reliable scale to evaluate anxiety and depression in Iranian anxious and depressed patients [42].Pain catastrophizing will be measured by the Pain Catastrophizing Scale (PCS). It has 13 items and three subscales (rumination, magnification, and helplessness). The range of total score is from 0 to 52, with higher scores indicating higher amounts of pain catastrophizing. The Persian version of PCS is valid and reliable in assessing pain catastrophizing in Iranian patients suffering from pain [43].Kinesiophobia will be assessed using the Tampa Scale. Tampa is a questionnaire with 17 items that evaluates fear of movement. Each item is scored on a scale of 1 to 4. The total score ranges from 17 to 68, with higher scores indicating greater fear of movement. The Persian version of the Tampa Scale has high reliability and validity for individuals with chronic pain [44, 45].Adherence to the treatment sessions in the telerehabilitation group will be evaluated by the calendar of the application and the sessions in which the participants will perform the exercises. In the control group, adherence will be assessed by the physical therapist recording the dates of the sessions on the participant’s treatment sheet. The time schedule of study was shown in Fig. 4.

**Fig. 4 Fig4:**
[figure not shown]
Standard protocol items: schedule of enrollment, interventions, and assessments (according to SPIRIT)

### Statistical methods

The statistical analysis will be performed by SPSS (Statistical Package for Social Science) version 26.0. Data will be reported as follows: mean, standard deviation, 95% confidence intervals, or frequency and percentiles. Descriptive statistics will be obtained on the demographic and clinical characteristics of the participants. Repeated-measures ANOVA (Analysis of Variance) will be used to determine the effects of the group assignments (telerehabilitation vs. face-to-face), the effects of time (baseline, post-intervention, and 1-month follow-up), and the group-by-time interaction for all the outcome measures. *P*-values less than 0.05 will be considered to be statistically significant in all tests. Missing data will be handled using an intention-to-treat (ITT) analysis approach.

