## Abstract

**Background:**

Patellofemoral pain syndrome (PFPS) is a common musculoskeletal condition in young and active adults. Exercise therapy is an essential part of rehabilitation in people with PFPS (PwPFPS). Telerehabilitation is an innovative treatment approach that has been used in several musculoskeletal conditions. This study aims to investigate the non-inferiority of telerehabilitation through a smartphone application, the *Vito App*, compared to face-to-face physical therapy on reducing pain and improving physical function, quality of life, and psychological factors.

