## Methods

### Study aims

The primary objective of this randomized controlled trial is to determine whether exercise therapy via telerehabilitation and mHealth is as effective as the same face-to-face physical therapy program in reducing pain and improving physical function and quality of life in PwPFPS.

The secondary objectives of this study are to evaluate the effectiveness of telerehabilitation in improving psychological factors, including anxiety, depression, kinesiophobia, and pain catastrophizing, and compare them to face-to-face physical therapy. We will also investigate the adherence of participants to the treatment plan. We hypothesize that telerehabilitation and face-to-face physical therapy will both be effective in pain reduction, and improving physical function, quality of life, and psychological factors; these two intervention methods have no superiority over each other.

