### Study design, randomization, and allocation

The present protocol is a non-inferiority, single-blinded, randomized controlled trial with two parallel groups (face-to-face physical therapy and telerehabilitation groups) and a 1:1 allocation ratio. The ethics committee of AJUMS (IR.AJUMS.REC. 1401.282) approved the protocol and it is registered (no: IRCT20201112049361N1.) in the Iranian Registry of Clinical Trials (IRCT). This study protocol follows the SPIRIT (Standard Protocol Items: Recommendations for Interventional Trials) checklist which is available as an additional file (Additional file 1) [36].

Participants will be randomly assigned to either the control group (face-to-face physical therapy) or the experimental group (telerehabilitation) using the stratified permuted block method (Fig. 1). Participants will be randomly assigned to groups based on age, sex, and level of activity as determined by the Tegner Activity Scale to ensure similarity of these variables. A computerized random allocation sequence with different block sizes (4 and 6) will be provided by an independent investigator who is not a member of the research team. An uninvolved party in the assessment will open the sealed envelopes.

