### Sample size

The sample size of 60 participants (30 per group) was determined using G*Power software (version 3.1.9.2) based on the input parameters of a power of 0.80, an α level of 0.05, and repeated-measures analyses of variance (ANOVAs) with within-between interaction statistical tests.

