Based on our hypothesis, participants in the telerehabilitation group and face-to-face physical therapy group will have the same improvements in clinical and psychological outcomes. If our results indicate that telerehabilitation is not inferior to face-to-face physical therapy, it can be an appropriate alternative for PwPFPS, due to its advantages over face-to-face physical therapy, such as the active role of the patients in managing their condition and the fact that there will be no need to refer directly to the physical therapist. PwPFPS living in rural or remote areas or those who do not have enough time to refer to physical therapy clinics can benefit from telerehabilitation methods. PwPFPS can also continue their exercise program as long as they want to use the *Vito App*, and the physical therapists can always have accessibility to their patient’s condition, and they can monitor their progress.

The present study has some limitations, such as the impossibility of blinding the participants and interventional physical therapists due to the nature of the intervention. Another limitation is the slow internet connection in Iran and application bugs that may hinder participants in the telerehabilitation group from using the application. Additionally, using a smartphone application may exclude participants who do not have access to the internet or smartphones.

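### The trial is designated non-inferiority, but its only stated test and its sample-size basis look for a difference and cannot establish non-inferiority

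*Protocol article*

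**What the plan says.** The abstract gives the aim: "This study aims to investigate the non-inferiority of telerehabilitation through a smartphone application". The section on study design, randomization and allocation repeats it: "The present protocol is a non-inferiority, single-blinded, randomized controlled trial with two parallel groups". The Discussion states the conclusion the trial hopes to reach: "If our results indicate that telerehabilitation is not inferior to face-to-face physical therapy, it can be an appropriate alternative for PwPFPS".

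The hypothesis at the end of Study aims is worded differently. It expects both treatments to be effective and adds that "these two intervention methods have no superiority over each other".

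Statistical methods names one inferential procedure: "Repeated-measures ANOVA (Analysis of Variance) will be used to determine the effects of the group assignments (telerehabilitation vs. face-to-face), the effects of time", and the group-by-time interaction, for all outcome measures. The threshold is that P-"values less than 0.05 will be considered to be statistically significant in all tests". Confidence intervals appear as a reporting format: "Data will be reported as follows: mean, standard deviation, 95% confidence intervals, or frequency and percentiles".

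Under Sample size, "The sample size of 60 participants (30 per group) was determined using G*Power software", with power 0.80, alpha 0.05 and a within-between interaction from a repeated-measures ANOVA.

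**The concern.** A non-inferiority trial tests the null hypothesis that the new treatment is worse by at least a margin, and claims success by rejecting it. The stated ANOVA tests the null hypothesis that the groups do not differ. Rejecting that null does not show non-inferiority, and neither does failing to reject it. The interaction F test over three visits and two groups has two degrees of freedom and no direction, so no P-value from it bears on whether telerehabilitation is worse by less than a stated amount.

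The result that fits the comparative half of the hypothesis is a non-significant one. In a trial of 60, a non-significant difference is quite likely even when telerehabilitation is materially worse, and fewer completers make it more likely still. If such a result were taken as non-inferiority, the recommendation of telerehabilitation as an alternative would rest on lack of precision.

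**Working it through.** **1. Aim against method.** The abstract, the design section and the Discussion all speak of non-inferiority. Statistical methods and Sample size both name a test for a difference. The text shown contains no rule that compares a confidence limit with a margin.

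**2. The plan's own figure.** For the within-between interaction, G*Power uses λ = f²·N·m/(1−ρ), with N = 60, m = 3 measurements and 2 groups. The article does not give the effect size f or the correlation ρ, so 60 can be neither confirmed nor refuted. It gives 80% power at f = 0.196, 0.166 or 0.128 for ρ = 0.3, 0.5 or 0.7. In every case that is power to detect a difference.

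**3. How often a real deficit would go undetected.** From the article: 30 per group, three visits, alpha 0.05. Assumed: unit SD, compound symmetry, ρ = 0.3, 0.5 or 0.7, no dropout, and telerehabilitation worse by d (in SD) at both later visits with no difference at baseline.

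- Interaction: f² = d²/18, so λ = (d²/18)·60·3/(1−ρ) = 10d²/(1−ρ), on 2 and 116 degrees of freedom.
- Group effect (mean of three visits): the difference is 2d/3 and the variance of a patient's mean is (1+2ρ)/3. So λ = (2d/3)² / [((1+2ρ)/3)·(2/30)] = 20d²/(1+2ρ), on 1 and 58 degrees of freedom.
- Under compound symmetry the two tests are independent, so the chance that neither is significant is the product.

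For d = 0.5, λ is 2.5/(1−ρ) for the interaction and 5/(1+2ρ) for the group effect:

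| ρ | λ interaction | non-significant | λ group | non-significant | neither significant |
|---|---|---|---|---|---|
| 0.3 | 3.57 | 63% | 3.13 | 59% | 37% |
| 0.5 | 5.00 | 51% | 2.50 | 66% | 33% |
| 0.7 | 8.33 | 28% | 2.08 | 71% | 19% |

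At d = 0.72, neither test is significant in about 10%, 7% and 2%. Simulation with 20,000 trials per setting agrees to within about one percentage point. Completer numbers are not in the article; with an assumed 26 per group, ρ = 0.5 and d = 0.5, the interaction is non-significant in 57% rather than 51%.

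**4. What 60 patients support as a non-inferiority trial.** Take a comparison at one visit, one-sided alpha 0.025, true difference zero and no dropout.

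- Standard error in SD units: √(2/30) = 0.258.
- Margin for 80% power: (1.960 + 0.842) × 0.258 = 0.72 SD.
- Power for a 0.5 SD margin: Φ(0.5/0.258 − 1.960) = Φ(−0.02) = 49%.
- Size needed for a 0.5 SD margin: 2 × (2.802/0.5)² = 62.8, so 63 per group and 126 in total.
- Half-width of the 95% confidence interval: 2.002 × 0.258 = 0.52 SD.

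**The case against.** The article condenses a fuller protocol, and an analysis plan may exist. A margin and a confidence-limit rule could be there, and the 95% intervals already planned are the tool a non-inferiority analysis needs. This stands in part: the absence of a margin from the article is not a finding in itself. But the article does state its test and its sample-size basis, and both conflict with its stated design. A margin held elsewhere would play no part in either.

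A reader might infer that the protocol commits to declaring non-inferiority whenever the ANOVA is non-significant. It does not say so. The Discussion is conditional and gives no rule. The inference is reasonable, because the hypothesis predicts no difference and no other route to the conclusion is described, but it supports only that a null result could be read that way.

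A reader might also infer that weaker data always favour the hoped-for conclusion. That goes too far. The hypothesis also requires both treatments to be effective, and the time effect is tested; small or noisy data make that half harder to meet. Only the comparative half has this weakness.

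Lastly, setting 51% beside the 2.5% of a proper test would mislead. Both the group and the interaction effects are tested, so the chance that neither is significant is the more relevant figure. The 2.5% applies only when the true deficit equals the margin, and the article gives none. At 0.72 SD, the margin that 60 patients could support, the chance is about 10%, 7% or 2%: above 2.5% at two of the three correlations, but far below 51%.

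**Conclusion.** The point holds as a contradiction between the stated design and the stated test and sample-size basis. As written, the analysis cannot establish non-inferiority whatever its P-values, so it must be corrected before the main conclusion can be drawn.

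The size of the risk depends on assumptions. If a non-significant result on both tests were taken as non-inferiority, a true deficit of 0.5 SD would pass in roughly one fifth to just over one third of trials for correlations from 0.7 down to 0.3. These figures assume compound symmetry, equal deficits at both later visits and full follow-up; the deficits and correlations are illustrative, not taken from the article. The mismatch itself depends on none of them.

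**What to change.** Before any between-group data are seen:

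1. Name one of the listed primary outcomes and one post-baseline visit for the non-inferiority claim, or state that all must pass. The article lists several primary outcomes (pain, the Kujala score, three functional tests, knee-related quality of life) and two later assessments, and singles out none.
2. Fix and register a margin for it in scale points, with its justification.
3. Estimate telerehabilitation minus face-to-face with a two-sided 95% confidence interval. Claim non-inferiority only if the unfavourable limit excludes the margin.
4. State that a non-significant ANOVA is not evidence of non-inferiority, and reword the comparative hypothesis in Study aims as one-sided.
5. Restate Sample size as the margin that 60 patients support: about 0.72 SD for 80% power, or about 49% power for 0.5 SD, before dropout.

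If no margin can be justified before unblinding, drop the non-inferiority claim from the aims, design and conclusion, and report the difference with its 95% confidence interval.

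Cost: amended wording in the protocol, registry entry and any analysis plan, with no new measurements. The stated 80% power may not apply to the non-inferiority question, and the trial may have to report an inconclusive result. If the justified margin is smaller than about 0.72 SD, 60 patients give less than 80% power, and the sponsor must either accept that or recruit more.

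### With baseline as a level of time, the group main effect carries only two thirds of the post-treatment difference; the interaction is undiluted but gives no directional estimate, and the plan does not say which decides

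*Protocol article*

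**What the plan says.** Under Statistical methods, the protocol article specifies the model and its group term: "Repeated-measures ANOVA (Analysis of Variance) will be used to determine the effects of the group assignments (telerehabilitation vs. face-to-face"). The same sentence then lists the other two effects to be tested, namely "the effects of time (baseline, post-intervention, and 1-month follow-up), and the group-by-time interaction for all the outcome measures". Time thus has three levels, the first being the pre-randomisation measurement. The section names no covariate.

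Under Sample size, the calculation is tied to one of these terms. A total of 60, with 30 in each arm, was obtained in G*Power for 80% power at a 5% level, and the procedure chosen there was "repeated-measures analyses of variance (ANOVAs) with within-between interaction statistical tests". No effect size, correlation between visits or sphericity correction is given.

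Under Study design, randomization, and allocation, the trial is declared a non-inferiority trial with "two parallel groups (face-to-face physical therapy and telerehabilitation groups) and a 1:1 allocation ratio". Allocation is made "using the stratified permuted block method". The factors used for stratifying are then given: "Participants will be randomly assigned to groups based on age, sex, and level of activity as determined by the Tegner Activity Scale". No non-inferiority margin is stated, and no passage says which of the three ANOVA effects answers the non-inferiority question.

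**The concern.** A non-inferiority conclusion needs a signed difference between the arms after treatment, with a confidence interval to set against a margin. The stated model offers two terms that involve group, and neither supplies this.

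- **Group main effect.** It is directional, but it averages over a visit at which no treatment effect can exist. Pulling the estimate toward zero is conservative in a superiority trial. In a non-inferiority trial it works in favour of the claim.
- **Group-by-time interaction.** It carries the full effect. With two groups and three times it is an F test on two degrees of freedom, with no sign and no estimate at a given visit. A non-significant result would not show non-inferiority.

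Baseline is measured on everyone before treatment. Using it as an outcome level rather than as a covariate gives up precision that 60 participants can ill spare. The stratification factors raise a smaller question of the same kind, which concerns the standard error only.

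**Working it through.** **1. The plan's own figure.** N = 60 can be neither reproduced nor refuted, because effect size f, visit correlation ρ and ε are not stated. For two groups, three measurements, ε = 1 and λ = f²·N·3/(1−ρ) (the G*Power default), N = 60 at 80% power implies f = 0.196, 0.166, 0.128 or 0.105 at ρ = 0.3, 0.5, 0.7 or 0.8. Under the program's other effect-size options it implies f of about 0.29. The sizing rests on the interaction, not on the group main effect.

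**2. What each term estimates.** Let d1 and d2 be the true differences at post-test and follow-up. The difference at baseline is 0 in expectation.

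- Group main effect: (0 + d1 + d2)/3.
- Mean post-treatment difference: (d1 + d2)/2.
- Ratio: (1/3)/(1/2) = 2/3, whatever d1 and d2 are.

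Relative to the post-test difference alone, the main effect keeps 67% if the effect persists, 50% if it halves by follow-up and 33% if it vanishes. A simulation (20,000 trials, ρ = 0.5, true difference 0.70 SD at both visits) gave 0.46 for the main effect, 0.69 for the change contrast (mean of the two post visits minus baseline) and 0.70 for ANCOVA. Only the main effect is diluted.

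**3. What the dilution could do.** Assume a margin of 0.5 SD and a true deficit of exactly 0.5 SD at both post visits. The main effect then centres on a deficit of 0.333 SD. Its variance factor is (1 + 2ρ)/3. At ρ = 0.5 this is 0.667, so SE = √(2 × 0.667/30) = 0.211. The chance that its 95% CI excludes the margin is about 1 − Φ(1.96 − 0.167/0.211) = 12%. For ρ from 0.8 to 0.3 it runs from about 10% to 14%, against the intended 2.5%. This applies only if the main effect is the deciding term.

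**4. Precision.** Assume unit SD, equal correlation ρ between visits and 30 per arm. SE = √(2v/30), with

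- change contrast: v = (1 + ρ)/2 + 1 − 2ρ;
- ANCOVA on the mean of the two post visits: v = (1 + ρ)/2 − ρ².

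At ρ = 0.5, v = 0.75 and 0.50, so ANCOVA has 1 − 0.50/0.75 = 33% less variance. Power is two-sided at 5% for an assumed difference of 0.5 SD at both post visits.

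| ρ (assumed) | v, change | v, ANCOVA | Variance saved | Power, group main effect | Power, 2-df interaction | Power, change contrast | Power, ANCOVA |
|---|---|---|---|---|---|---|---|
| 0.3 | 1.05 | 0.56 | 47% | 41% | 37% | 46% | 72% |
| 0.5 | 0.75 | 0.50 | 33% | 34% | 49% | 59% | 77% |
| 0.7 | 0.45 | 0.36 | 20% | 30% | 72% | 81% | 89% |
| 0.8 | 0.30 | 0.26 | 13% | 28% | 89% | 94% | 96% |

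The last two columns give the fair comparison for baseline handling, since both are one-degree-of-freedom contrasts of the same effect. The power figures are superiority power and serve only as a scale for precision.

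**5. Stratification factors.** Omitting a balanced factor leaves the expected difference unchanged. If the factors explain a share R² of outcome variance, the model SE is too large by 1/√(1 − R²) − 1. For assumed shares of 5%, 10% and 20% this is 2.6%, 5.4% and 11.8%. The documents give no share.

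**The case against.** The strongest reply is that the same sentence plans the group-by-time interaction, and the sample size section singles out that term. The interaction is undiluted, and testing it in a randomised trial is a valid, unbiased assessment of the effect on change. This stands. A reader might infer that the planned analysis as a whole shrinks the treatment effect by a third. The documents do not support that, because the shrinkage belongs to one of the listed terms and nothing says that term decides.

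It can also be said that the efficiency case depends on the comparator. Setting ANCOVA against the group main effect at ρ = 0.5 suggests a threefold gain in sample efficiency. That uses the weakest comparator and a single assumed correlation. Against the change contrast the variance ratio is 1.5 at ρ = 0.5 and 1.15 at ρ = 0.8. Part of the gap between 49% and 77% power comes from spending two degrees of freedom rather than one. This too stands, and is why the size is given as a range against the change contrast.

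Finally, this is a condensed article and a separate analysis plan may exist. Covariates could be listed there, so the absence of the stratification factors is weak evidence of a decision. A reader might also think their omission helps to shrink the effect; it does not. The three-level time factor is different, because the article states it outright and a later plan that adjusted for baseline would have to change it.

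What the objection does not answer is that the interaction test gives no signed difference with an interval at a named visit.

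**Conclusion.** The point holds in a limited form. The group main effect, as specified, estimates exactly two thirds of the mean post-treatment difference. This follows from randomisation and needs no numerical assumption. It would favour a non-inferiority conclusion if it were the deciding term, which the documents neither say nor exclude. The interaction is undiluted but cannot by itself deliver a non-inferiority conclusion.

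The loss of precision against baseline adjustment is 13% to 47% of the variance for ρ from 0.8 to 0.3. It rests on an assumed correlation, equal correlation across visits and complete data on 30 per arm. It is modest if repeated measurements are highly correlated and substantial if they are not. The margin of 0.5 SD and the difference of 0.5 SD used above are illustrative assumptions. The stratification factors are a secondary matter, whose effect on the standard error cannot be computed from the documents. This should be changed, but it does not invalidate the trial.

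**What to change.** Replace the three-level analysis in Statistical methods as follows.

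- Use post-test and 1-month follow-up as the outcome visits. Fit group, visit and group-by-visit, with the baseline value of the same outcome as a covariate.
- Name the primary visit. Report there the adjusted telerehabilitation minus face-to-face difference with its 95% CI, and state that this estimate answers the non-inferiority question.
- Do not use the three-level group main effect for inference.
- As a secondary step, enter age, sex and Tegner level as covariates; age and Tegner level may be continuous.

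The cost is a change of wording and about four degrees of freedom. Baseline values are already collected at pre-test, and the other covariates for randomisation. The change should be recorded before outcomes are compared by group.

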### Outcome measures

The outcome measures will be assessed in three phases: pre-test, post-test (after 6 weeks and 18 sessions), and follow-up (1 month after the final session) to evaluate the mid-term effects of the intervention. The same physical therapist ([name]), who is blinded to the participant’s group allocation, will evaluate the outcome measures in every phase in a random order. All assessments were conducted at the Rehabilitation Research Center, AJUMS, Ahvaz, Iran.

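### Intention-to-treat is named as the missing-data method, but it supplies no values, and the only model named would in its standard form drop anyone who misses a visit

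*Protocol article*

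**What the plan says.** The Statistical methods section of the protocol article gives the software ("The statistical analysis will be performed by SPSS (Statistical Package for Social Science) version 26.0") and a single model: "Repeated-measures ANOVA (Analysis of Variance) will be used to determine the effects of the group assignments". The model also covers "the effects of time (baseline, post-intervention, and 1-month follow-up), and the group-by-time interaction for all the outcome measures". The paragraph closes on missing data: "Missing data will be handled using an intention-to-treat (ITT) analysis approach". It names no imputation method, no likelihood-based model and no sensitivity analysis.

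On visit timing, the Outcome measures section has "post-test (after 6 weeks and 18 sessions), and follow-up (1 month after the final session". The Methods part of the Abstract uses calendar wording only: the post-test follows the six weeks of intervention, and the follow-up comes one month after the intervention ends.

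Two other places matter. Study design, randomization, and allocation calls the trial non-inferiority. The limitations at the end of the Discussion say that slow internet and application faults may hamper participants in the telerehabilitation group.

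**The concern.** The missing-data sentence answers a different question from the one it raises. A participant can be kept in the allocated arm on paper and still have no follow-up value, and the intention-to-treat principle does not say what the analysis then does. That is left to the model. Standard repeated-measures ANOVA in SPSS takes one row per participant and needs all three visits. Someone with a baseline and a post-test but no follow-up is lost completely, including the post-test that was observed.

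Two things are at stake. The first is precision: each missed visit costs a whole participant, for every outcome. The second is bias. In a non-inferiority trial, an analysis that removes the poorer results from the experimental arm makes that arm look closer to the control. The protocol itself gives a reason why difficulties could arise in the app arm.

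**Working it through.** **Step 1. What the shown text leads to.**

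| Element | Protocol | Consequence |
|---|---|---|
| Population principle | Intention-to-treat | Everyone randomised, as allocated |
| Model | Repeated-measures ANOVA, SPSS 26.0 | Standard form: one row per participant |
| Visits | Baseline, post-intervention, 1-month follow-up | All three values required |
| Imputation before the model | None named | Incomplete rows dropped |

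The first row and the last can both be met only if values are imputed beforehand or a different procedure (such as SPSS MIXED) is used. The section mentions neither.

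**Step 2. The plan's own figure.** The Sample size section gives 60 participants (30 per group), power 0.80, α 0.05 and a within-between interaction test. It states neither an effect size f nor a correlation ρ, so 60 can be neither confirmed nor refuted. I therefore take 60 as giving exactly 80% power with complete data and solve for f.

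For k = 2 groups, m = 3 visits and sphericity:
- λ = f² × N × m / (1 − ρ)
- df1 = (k − 1)(m − 1) = 2
- df2 = (N − k)(m − 1)

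With N = 60 and ρ = 0.5 (assumed), power 0.80 needs f = 0.1657. Then λ = 0.1657² × 60 × 3 / 0.5 ≈ 9.89, with df2 = 116. For ρ = 0, 0.3 and 0.7 the solved f is 0.234, 0.196 and 0.128. In each case λ is again 9.89, so the powers in step 3 do not depend on the assumed ρ.

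**Step 3. Power with fewer complete cases.** For the same effect, λ falls in proportion to N.

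| Complete cases | Lost from 60 | λ | df2 | Power |
|---|---|---|---|---|
| 60 | 0% | 9.89 | 116 | 0.80 |
| 54 | 10% | 8.90 | 104 | 0.75 |
| 48 | 20% | 7.91 | 92 | 0.70 |
| 42 | 30% | 6.92 | 80 | 0.63 |

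The loss rates are assumptions. How missed visits turn into lost participants depends on their overlap. Suppose 10% miss each of the two post-baseline visits. If the misses are independent, 1 − 0.9² = 19% are dropped and 60 × 0.81 = 48.6 remain. If the same people miss both, 10% are dropped and 54 remain.

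**Step 4. Possible bias, under assumptions.** A simulation of 4,000 trials used these inputs, none of them from the protocol:
- VAS SD 2, ρ = 0.5, no true difference between arms;
- telerehabilitation: log-odds of missing the follow-up = −2.0 + 0.8 × (post-test pain − 3.5);
- control: 5% lost at random.

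On average about 53 of 60 participants were complete. The complete-case difference at post-test was −0.46 VAS points in favour of telerehabilitation, against about 0 with everyone included. That is 0.46 / 2 = 0.23 SD, although every post-test value had been observed. If the selective loss were in the control arm instead, the sign would reverse by symmetry.

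**The case against.** **Is it a flat contradiction?** A reader might infer that the two statements cannot both be carried out. The documents do not support that. The section names SPSS but no procedure, and never says that cases will be dropped. Imputing first, or fitting the model in SPSS MIXED, would avoid deletion. One may add that a journal article can leave the method to a fuller plan. The conditionality stands. The last argument does not remove the point: the sentence does address missing data, and names something that cannot handle it.

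**Does a participant who stops early have no defined post-test?** The 18-session wording tempts one to say so. The Abstract, however, places the post-test after six weeks, the Outcome measures section also gives six weeks, and 18 sessions is simply three per week for six weeks. The schedule figure is not shown. What remains is a wording mismatch.

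**Is the result biased towards the app?** This cannot be asserted. The Discussion supports app-arm difficulties, but the Background and Discussion also expect better adherence with telerehabilitation, and control participants must attend the clinic. Outcomes are measured at the research centre, so an app fault need not cause a missed assessment.

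**Can the bias be set against the non-inferiority margin?** No. The article states no margin, so any such fraction would rest on a figure supplied by the reader.

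**Is a mixed model the cure?** Only in part. It is valid when missingness depends on observed data. Multiple imputation before the ANOVA would answer the same objection.

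**Conclusion.** The point holds in this form. The missing-data rule is wrongly stated. With the only model named, run in its standard form on unimputed data, the analysis is complete-case under an intention-to-treat label. This follows from how the method works and needs none of the figures above.

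If 60 gives exactly 80% power, power falls to about 75% with 54 complete cases and about 70% with 48. These are powers for the interaction test of difference, not for a non-inferiority comparison, and the loss rates are assumed. Bias in favour of telerehabilitation is plausible if app users who do worse are lost, but its direction and size cannot be established from the protocol. The visit wording is a secondary matter of alignment.

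**What to change.** 1. Replace the repeated-measures ANOVA with a likelihood-based linear mixed model for repeated measures (SPSS MIXED, unstructured covariance). Include all randomised participants in their allocated arm, with every available visit.
2. Delete the sentence that offers intention-to-treat as a missing-data method. State instead the analysis set and the missing-at-random assumption on which the model relies.
3. Add a delta-adjusted sensitivity analysis in which missing telerehabilitation values are made worse over a stated range of deltas. A range is needed because the article gives no margin to fix a single value.
4. Align the Outcome measures wording (18 sessions, final session) with the Abstract's time-based wording. Outcomes are then collected at the same times from participants who stop early. Attend to this first, because recruitment is described as ongoing and values not collected cannot be recovered later.

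The cost is a change of wording, a different procedure in the same software, a small amount of extra analysis, and some effort to assess people who have stopped their sessions.
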